#### Process evaluation

During the planned regular meetings with members of the local ASB teams to report results and feedback, we will evaluate the introduced interventions. By exchanging thoughts and experiences on the implemented interventions, we will be able to determine what intervention(s) will work best in daily practice. For the process evaluation, we will evaluate the deimplementation strategy adherence and compliance. Therefore, all elements of the deimplementation strategy will be explored in all participating hospitals. We will award the hospitals with feedback points for all elements of the deimplementation strategy.^27^ For example, points will be given for the number of persons present at the planned meetings and for every strategy that is implemented.

#### Economic evaluation

We will primarily perform a cost-effectiveness analysis, in which we evaluate the cost effectiveness ratio (CER) (CER=cost of deimplementation/healthcare cost reduction). Our goal was to achieve a reduction in urine culture, urinalysis and antimicrobial prescriptions, and thereby a reduction in costs. The costs of our deimplementation strategy will be divided in non-recurrent study-related costs and recurrent de-implementation-related costs. Non-recurrent study-related costs include material costs, developmental costs of the deimplementation strategy and costs of evaluation of the deimplementation. Recurrent costs include the costs to introduce the deimplementation strategy, such as time of the extra meetings of the ASB team and time invested by the local champion. For feasibility reasons, we will use the number of all urine cultures, urinalyses and antimicrobial prescriptions, representing the main cost benefits due to our strategy. The costs for urine cultures, urinalyses and antimicrobials used in the analyses will be based on Dutch guideline on healthcare economic evaluations.^28^ The result of the cost-effectiveness analysis will be used in a budget impact analysis to assess the financial impact on the hospital’s budget to implement and sustain the deimplementation strategy.

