## Discussion

This study protocol describes the design, deimplementation strategy and process evaluation to reduce overtreatment of ASB in the daily practice of emergency medicine. Our deimplementation strategy could prevent the use of unnecessary urine diagnostics and subsequent inappropriate treatment of ASB, improve healthcare quality, lower the increase in antimicrobial resistance and save costs. If proven to be (cost) effective, this study could provide a nationwide strategy to reduce overtreatment of ASB.

In our study, we will not evaluate the clinical outcome of our strategy, including potential clinical benefits, such as reduced side effects of antibiotics, since previous studies have already shown that ASB in non-risk patients does not lead to an increased risk of symptomatic UTI and that it is safe to not treat ASB.^29 30^

By using a stepped-wedge cluster randomised design, we will be able to compare the outcomes within a cluster between the time intervals in which a cluster received the control and the interventions. Furthermore, our intervention will be enrolled in a systematic manner and eventually will be introduced in all participating hospitals. A novel part of our study compared with previous studies that aimed to reduce overtreatment of ASB is that we will be using local champions in each hospital and adjust the intervention based on the local situation.

A limitation of stepped wedge designs is that this requires larger sample sizes, as patients’ characteristics may be similar within one cluster. By randomisation of the start time of the clusters, we intend to balance these important characteristics. However, this cannot be ensured with our relatively small number of clusters.^31^ Another possible limitation is that we will not prospectively assess clinical symptoms ourselves and are limited to documentation of symptomatology in patient files. This might overestimate the number of patients with asymptomatic bacteriuria in the baseline and intervention periods. Since this should be similar in the baseline and intervention periods, we do not expect that this will influence our results. Furthermore, we cannot evaluate the impact of an individual intervention. However, we expect that our deimplementation strategy is low cost and well suitable for broad-scale implementation.

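### The primary economic measure is labelled a cost-effectiveness ratio but is a cost-to-savings ratio: above 1 it cannot show whether the net cost is worth paying, and its numerator is not fixed

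*Protocol article*

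**What the plan says.** All of this is in the protocol article, mainly in the section Economic evaluation.

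- **Type of analysis.** "We will primarily perform a cost-effectiveness analysis", with the measure given as the "cost effectiveness ratio (CER) (CER=cost of deimplementation/healthcare cost reduction".
- **Aim.** The section seeks a "reduction in urine culture, urinalysis and antimicrobial prescriptions, and thereby a reduction in costs".
- **Savings.** For feasibility, "we will use the number of all urine cultures, urinalyses and antimicrobial prescriptions, representing the main cost benefits due to our strategy". Prices come from the Dutch guideline on economic evaluations.
- **Costs.** "The costs of our deimplementation strategy will be divided in non-recurrent study-related costs and recurrent de-implementation-related costs". The non-recurrent group holds material costs, "developmental costs of the deimplementation strategy and costs of evaluation of the deimplementation". The recurrent group holds the cost of introducing the strategy, such as team meetings and the local champion's time.
- **Use of the result.** It "will be used in a budget impact analysis to assess the financial impact on the hospital’s budget to implement and sustain the deimplementation strategy". The Discussion adds: "If proven to be (cost) effective, this study could provide a nationwide strategy to reduce overtreatment of ASB". The Abstract (Ethics and dissemination) makes nationwide use depend on the same condition.

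The clinical effect is defined elsewhere. Under Primary and secondary endpoints it is the percentage of ASB patients without risk factors who receive antimicrobials. The same section plans culture and urinalysis numbers per 1000 ED patients.

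**The concern.** A cost-effectiveness ratio sets net cost against a unit of effect, so that a payer can judge whether the effect is worth its price. The stated formula divides money spent by money saved and so answers a different question: whether the strategy pays for itself. That is useful, but the two questions have the same answer only when the strategy saves money.

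A stewardship programme can be worth having at a modest net cost, because fewer unnecessary antimicrobial courses have value beyond their price. The Introduction and Discussion argue this themselves, citing resistance and quality of care. If the ratio comes out above 1, the plan has no stated measure for judging that case, yet the claim of being (cost) effective is tied to nationwide use.

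The numerator is a second problem. Study evaluation costs appear under the costs of the strategy, and the text does not say whether the ratio uses both cost groups or only the recurrent one. A hospital adopting the strategy later would not pay to evaluate this trial.

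**Working it through.** The article gives no cost, price, threshold or expected ratio, so there is no economic figure to reproduce. All amounts below are assumed and carry no unit. They show how the measure behaves, not what the trial will find.

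**Notation.** C = strategy cost, S = healthcare cost reduction, n = ASB overtreatments avoided.

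- Plan's ratio: CER = C / S.
- Net cost per overtreatment avoided: (C − S) / n = S × (CER − 1) / n.

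The second line shows what the plan's ratio carries and what it lacks. For S above 0 it fixes the sign of the net cost, with break-even at 1. It says nothing about n.

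**1. What the ratio can and cannot show (C = 3000)**

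| S | n | CER | (C − S) / n |
|---|---|---|---|
| 6000 | 100 | 3000/6000 = 0.5 | −3000/100 = −30 |
| 3000 | 10 or 100 | 3000/3000 = 1.0 | 0 |
| 2000 | 100 | 3000/2000 = 1.5 | 1000/100 = 10 |
| 2000 | 10 | 3000/2000 = 1.5 | 1000/10 = 100 |
| −500 | 50 | 3000/(−500) = −6.0 | 3500/50 = 70 |

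In the first row the strategy costs less and avoids overtreatment, which is dominance, and the ratio is enough. In the third and fourth rows the ratio is the same while the price per overtreatment avoided differs tenfold. Equal savings with different n are possible because S also counts cultures and urinalyses, and covers all of them rather than only those that end in ASB treatment. The last row shows that a value numerically below 1 can be a loss, so the saving region is between 0 and 1. At S = 0 the ratio is undefined.

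**2. Which costs enter the numerator (recurrent costs 4000, S = 10000)**

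Recurrent costs only: 4000/10000 = 0.4. With non-recurrent costs added:

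| Non-recurrent costs added | CER |
|---|---|
| 2000 | 6000/10000 = 0.6 |
| 4000 | 8000/10000 = 0.8 |
| 8000 | 12000/10000 = 1.2 |
| 16000 | 20000/10000 = 2.0 |

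The ratio passes 1 once non-recurrent costs exceed 10000 − 4000 = 6000. In this illustration the unstated choice decides whether the strategy is reported as cost-saving.

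**3. What the number avoided has to count**

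The planned effect model concerns the percentage treated among ASB patients. The strategy also aims at less testing, so fewer ASB cases may be found. Let a0 and a1 be ASB cases found per 1000 ED patients under control and intervention. Take the proportions treated from Sample size, 0.450 and 0.225.

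- Overtreatments avoided per 1000 ED patients = 0.450 × a0 − 0.225 × a1 = 0.225 × a0 + 0.225 × (a0 − a1).

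Applying the fall in percentage (0.225) to the control caseload a0 gives only the first term. It misses 0.225 overtreatments for each ASB case no longer found. The number avoided therefore has to be a rate per 1000 ED patients.

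**The case against.** The strongest defence is that the ratio fits the section's own aim, which is to lower costs through fewer tests and prescriptions. If it lies between 0 and 1 and the separate effect analysis shows less overtreatment, the strategy is cheaper and better, and no cost per unit of effect is needed. This stands. A reader might infer that the measure can never support a claim of cost-effectiveness; the documents do not support that.

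Nor is the ratio wholly without effect. An avoided overtreatment is an avoided prescription, and prescriptions are priced into the savings. What is absent is the clinical effect in natural units.

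A reader might also infer that evaluation costs are in the numerator. The heading sentence, which speaks of the costs of the strategy, points that way. The split into study-related and de-implementation-related costs, and a numerator named cost of deimplementation, point the other way. Only the ambiguity is established.

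A further tempting step is that changes in ED volume or calendar time would be booked as savings. That would need raw, unadjusted counts. The economic section mentions numbers of tests and prescriptions but does not say how they are compared, and test rates per 1000 ED patients are already planned as secondary endpoints. Likewise, it does not follow that the budget impact analysis is unsound. It properly works in money, and the recurrent/non-recurrent split serves it.

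Finally, net cost per overtreatment avoided has weaknesses of its own. It is undefined at zero effect, and its negative values are ambiguous. Zero savings is therefore no strong argument against the plan's ratio. The argument that holds is the missing unit of effect above 1.

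That the article condenses a fuller plan does not remove the point on the label, because the formula is stated and does not match its name.

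**Conclusion.** The point holds in limited form. The measure named a cost-effectiveness ratio is a cost-to-savings ratio. It can show that the strategy saves money. When it exceeds 1 it cannot show whether the net cost is reasonable, and in that case the conclusion of being (cost) effective has no stated basis. Whether study evaluation costs belong to the numerator is left open, and that choice can move the ratio across 1.

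The size cannot be estimated from the article. The illustrations (a tenfold difference in cost per overtreatment avoided at the same 1.5, and a move from 0.4 to 1.2) rest on assumed amounts. The primary endpoint, the effect analysis and the sample size are unaffected. The change is worth making because a roll-out claim is attached to the economic result.

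**What to change.** 1. Make the main economic measure the incremental net cost, strategy cost minus savings, per ASB overtreatment avoided. Report net cost and number avoided separately as well, so that zero or negative values can be read.
2. Derive the number avoided from an effect adjusted for hospital and time, expressed per 1000 ED patients so that cases prevented by less testing count.
3. Show uncertainty by a method suited to five clusters, or by a stated sensitivity range. A bootstrap that resamples five hospitals is not reliable.
4. Keep cost divided by savings as a secondary measure, named cost-to-savings ratio or return on investment.
5. State which costs enter each measure. For the roll-out perspective use the recurrent de-implementation costs, and show study evaluation costs separately.
6. Base test savings on the rates per 1000 ED patients already planned under Primary and secondary endpoints.

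The cost is some rewording and a small amount of extra analysis, using data that are already planned.

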## Ethics and dissemination

Ethical approval was obtained on 13 December 2019 from the medical ethics research committee of the Academic Medical Centre (Amsterdam, the Netherlands), with a waiver for informed consent. Local feasibility was obtained by the local institutional review boards of all participating hospitals. This trial is registered at Netherlands Trial Register, trialregister.nl/trial/8242. All relevant results of our study will be disseminated through publications in peer-reviewed journals and presentations at relevant (scientific) conferences. No identifiable patient data will be disseminated.

### Patient and public involvement

This research will be performed without patient involvement. Patients will not be invited to comment on the study design and will not be consulted to develop patient-relevant outcomes or interpret the results. Patients will not be invited to contribute to the writing or editing of this document for readability or accuracy.

### Data availability

Data collected from this study, including deidentified individual participant data, will be made available on publication to investigators whose proposed use of the data has been approved by an independent review committee identified for this purpose. Proposals should be directed to the chief investigator [name] ([contact]); to gain access, data requestors will need to sign a data access agreement.

## Discussion

This study protocol describes the design, deimplementation strategy and process evaluation to reduce overtreatment of ASB in the daily practice of emergency medicine. Our deimplementation strategy could prevent the use of unnecessary urine diagnostics and subsequent inappropriate treatment of ASB, improve healthcare quality, lower the increase in antimicrobial resistance and save costs. If proven to be (cost) effective, this study could provide a nationwide strategy to reduce overtreatment of ASB.

In our study, we will not evaluate the clinical outcome of our strategy, including potential clinical benefits, such as reduced side effects of antibiotics, since previous studies have already shown that ASB in non-risk patients does not lead to an increased risk of symptomatic UTI and that it is safe to not treat ASB.^29 30^

By using a stepped-wedge cluster randomised design, we will be able to compare the outcomes within a cluster between the time intervals in which a cluster received the control and the interventions. Furthermore, our intervention will be enrolled in a systematic manner and eventually will be introduced in all participating hospitals. A novel part of our study compared with previous studies that aimed to reduce overtreatment of ASB is that we will be using local champions in each hospital and adjust the intervention based on the local situation.

A limitation of stepped wedge designs is that this requires larger sample sizes, as patients’ characteristics may be similar within one cluster. By randomisation of the start time of the clusters, we intend to balance these important characteristics. However, this cannot be ensured with our relatively small number of clusters.^31^ Another possible limitation is that we will not prospectively assess clinical symptoms ourselves and are limited to documentation of symptomatology in patient files. This might overestimate the number of patients with asymptomatic bacteriuria in the baseline and intervention periods. Since this should be similar in the baseline and intervention periods, we do not expect that this will influence our results. Furthermore, we cannot evaluate the impact of an individual intervention. However, we expect that our deimplementation strategy is low cost and well suitable for broad-scale implementation.
